## Abstract

**Abstract:**

**Introduction:**

School environments that encourage children to be physically active can embed lifelong positive health behaviours and contribute towards reducing health inequalities. The Health and Activity of Pupils in the Primary Years (HAPPY) study aims to: (1) explore the extent to which the WHO criteria for creating active school environments are implemented by primary schools and (2) examine associations between active school environments and children’s physical activity, mental health and educational performance.

**Methods and analysis:**

The HAPPY study is a quasi-experimental study comprising: (1) a survey of state-funded Greater London primary schools to identify implementation of the WHO’s six criteria and (2) a cross-sectional study to examine associations between schools’ active environment score (derived from the school survey) and pupils’ physical activity, mental health and educational performance. For our cross-sectional study, we will recruit up to 1000 year-three children (aged 7–8 years). Our primary outcome is accelerometer (GENEActiv) assessed physical activity, our secondary outcomes are parent-reported child mental health (Strengths and Difficulties Questionnaire) and teacher-reported educational performance (age-related expectations). Using multilevel mixed-effects regression models, we will examine associations between the active environment score and physical activity. Physical activity will be included as a measure of acceleration and also different intensities (light, moderate, vigorous). We will repeat this analysis to examine associations between the active environment score and mental health and educational performance. We will adjust for school characteristics and area-level deprivation and include pupil characteristics (eg, sex, ethnic group) as covariates. Clustering at the school level will be included as a random effect.

**Ethics and dissemination:**

Ethical approval has been obtained from Imperial College Research Ethics Committee (ref: 6800895). Findings will be disseminated through a summary report to all participating schools, peer-reviewed publications, presentations at national and international conferences and National Institute for Health and Care Research policy briefings.

STRENGTHS AND LIMITATIONS OF THIS STUDYThis protocol describes an observational quasi-experimental study to understand schools’ policies and practices for creating active school environments.By targeting all schools in Greater London, the survey will reflect a diverse urban conurbation and multi-ethnic primary school population.The use of accelerometers in the cross-sectional study will provide accurate measures of physical activity and avoid potential bias of self-reporting.Multilevel mixed-effects regression models will include clustering of pupils by school, to allow for accurate standard errors and parameter estimates when testing for associations between active environment scores and outcomes.Low response rates to the school survey may affect generalisability of findings to other diverse urban conurbations.

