The aim of our study is to explore the implementation of physical activity policies based on the WHO’s recommendation of a whole-school approach and to examine associations between a derived active environment score and children’s physical activity, mental health and educational performance.

Our aim is underpinned by the following research questions:

Which of the WHO’s policies and practices are currently implemented by primary schools in Greater London to create a physically active school environment?Do schools with a higher active school environment score have better physical activity, mental health and educational performance among their pupils?How equitable is the level of an active school environment across subgroups of children including those living in deprived areas, minority ethnic groups and those with disabilities?

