### Study setting and population

Our school survey was distributed to all state-funded primary schools in Greater London (n=1826). For our cross-sectional study, primary schools were recruited to participate, through which we invited children in year three (aged 7–8 years; one of the age groups identified as the least active in the primary school years^12^) and their parent/guardian to participate. All children in year three were eligible for participation, but participation was optional. Completion of both consent (adult) and assent (child) was required to participate in the study. Our target, based on our previous work,^14^ was to recruit up to 1000 children from approximately 40 schools across Greater London.

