### Procedure

#### School survey

Details of all state-funded primary schools were derived from a schools database that we created previously^15^ and updated with details to include new schools. All school details are publicly available from the UK government website.^16^ We distributed paper versions of our survey by post (including a freepost envelope to return the completed survey) in November 2023 and sent four reminders by email (January 2024, April 2024 and July 2024) to encourage survey completion; a final reminder, by post, took place in September 2024 (see figure 1). The survey (both by post and email) was addressed for the attention of the head teacher, but any teacher best placed to answer the questions could complete the survey. The survey closed in December 2024.

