### Potential strengths and limitations

A key strength of the HAPPY study is that it is conducted in a diverse, multiethnic urban conurbation which will identify whether physical activity promotion and equitability differ across Greater London boroughs with different levels of deprivation. Findings will therefore potentially be representative of other diverse urban conurbations. A further strength is accelerometer assessed physical activity which will provide more accurate estimates of daily physical activity minimising the recall bias of participant self-report methods that typically lead to overestimates of physical activity.^37^ Furthermore, accelerometers worn on the non-dominant wrist and processing the raw accelerometer data in 5 s epochs will reduce effects of short intermittent outbursts (eg, random arm movements) included in the average acceleration values when calculating time spent in different PA intensities. This provides a more accurate measure of total PA. Potential limitations of the study include the cross-sectional design of the study; we will only be able to assess associations rather than cause and/or effect. Additionally, schools may not be representative of all schools in Greater London.

Global policies are focused on reducing physical inactivity by 15% by 2030,^2^ where inequalities may be best addressed during childhood when healthy behaviours can be embedded. The results of our study will therefore be of interest to public health policymakers, teachers, parents and children. The findings from the HAPPY study will determine how physically active school environments are associated with children’s physical activity, mental health and educational performance. This study has the potential to inform national strategies for the promotion of physical activity in schools, targeting all children and contributing towards reducing physical activity inequalities in child health.

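### The representativeness claim for the school survey rests on who was invited, and the low-response limitation names other conurbations instead of Greater London, the target of research question 1

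*Protocol article*

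**What the plan says.** The strengths and limitations list in the Abstract of the protocol article (printed under Ethics and dissemination) makes two statements about the survey. The strength reads: "By targeting all schools in Greater London, the survey will reflect a diverse urban conurbation and multi-ethnic primary school population". The limitation reads: "Low response rates to the school survey may affect generalisability of findings to other diverse urban conurbations".

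Research question 1, in the Introduction, asks which WHO "policies and practices are currently implemented by primary schools in Greater London". Study setting and population gives the number of schools sent the survey as 1826. Procedure, School survey, states that "Details of all state-funded primary schools were derived from a schools database" which the team had built earlier and updated, and that school details are public.

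The Discussion, under Potential strengths and limitations, says: "Findings will therefore potentially be representative of other diverse urban conurbations". It later concedes: "Additionally, schools may not be representative of all schools in Greater London". Statistical analysis lists school characteristics to be reported: size, ethnic mix, Ofsted rating, free school meals and area deprivation.

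**The concern.** The strength bullet derives what the survey describes from who received it. Completion was voluntary, so the results describe the schools that answered. A school that takes physical activity seriously may be readier to answer a questionnaire about it, and implementation of the WHO criteria would then look more common than it is. A confidence interval around the responders' figure would not show this.

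The limitation bullet places the problem one step too far out. Non-response threatens the statement about Greater London before it threatens any extension to other cities, and Greater London is the population that research question 1 names. The findings are meant for policy briefings, where a prevalence for Greater London schools would probably be read at face value.

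**Working it through.** **Side by side.** The Abstract's strength claims that the survey reflects the Greater London school population. The Abstract's limitation allows that low response may weaken transfer to other conurbations. The Discussion allows that schools may not represent Greater London, without saying whether it means survey schools or cross-sectional schools and without linking this to non-response. The first and third statements need reconciling, and the second does not cover the population in research question 1.

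**No figure to reproduce.** The article gives no survey response rate, expected number of responders or survey precision. What follows is illustration under stated assumptions.

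**Inputs**
- N = 1826 schools invited (Study setting and population).
- Response rate r: not given; assumed 10% to 90%.
- Gap d between responders' and non-responders' prevalence: not given; assumed 10 points. A 20-point gap doubles each bias.
- Prevalence of 50% for the margin of error, where the margin is widest.

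**Bias.** The population prevalence is r × (responders) + (1 − r) × (non-responders). The unweighted responder figure therefore differs from it by (1 − r) × d.

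**Margin.** 1.96 × √[0.25/n × (N − n)/(N − 1)], with n = rN rounded. For r = 20%, n = 365: 1.96 × √[0.25/365 × 1461/1825] = 4.6 points.

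| Response | n | Bias, d = 10 | 95% margin | Gap at which bias equals margin |
|---|---|---|---|---|
| 10% | 183 | 0.9 × 10 = 9 | 6.9 | 6.9/0.9, about 8 |
| 20% | 365 | 0.8 × 10 = 8 | 4.6 | 4.6/0.8, about 6 |
| 50% | 913 | 0.5 × 10 = 5 | 2.3 | 2.3/0.5, about 5 |
| 90% | 1643 | 0.1 × 10 = 1 | 0.8 | 0.8/0.1, about 8 |

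At low to moderate response, a gap of this size puts the bias well outside the margin. At 90% response both are about 1 point and of little practical weight.

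**What weighting can do.** Assume two equal groups of schools with true implementation of 70% and 50%, so 60% overall, and let the first group respond at twice the rate of the second.
- Unweighted: (2 × 70 + 1 × 50)/3 = 63.3%. Weighted to the list of schools: (70 + 50)/2 = 60.0%. The bias is removed.
- Now let implementing schools also be 1.5 times as likely to respond within each group, keeping the 2:1 ratio of responders between groups. The responder figures become 0.7 × 1.5/(0.7 × 1.5 + 0.3) = 77.8% and 0.5 × 1.5/(0.5 × 1.5 + 0.5) = 60.0%. Unweighted: (2 × 77.8 + 60.0)/3 = 71.9%. Weighted: (77.8 + 60.0)/2 = 68.9%. Most of the bias remains.

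**The case against.** The strongest reply is that the article already concedes the point: the Discussion says that schools may not be representative of Greater London, and low response appears as a limitation directly after the strengths. The team also worked to raise response, with freepost return, repeated reminders, and paper and online formats. This stands in part. The concession exists, but the Abstract's claim was not brought into line with it, and the limitation that names survey response points at the wrong population.

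Three stronger readings are tempting, and the document does not support them.

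- **That the plan expects low response.** It says only that low response may affect generalisability, and gives no rate.
- **That results will be unweighted, and that this is an error.** Nothing says so. A condensed article may leave a non-response comparison and weighting to the full analysis plan, so their absence is not a fault here. Nor does holding the list of schools mean that the bias can be corrected: the database variables are not listed, and attitude to physical activity would not be expected among public school details.
- **That research question 3 is biased if response varies with deprivation.** Variation with deprivation alone does not bias a comparison across deprivation levels. That would need response to depend on the score within those levels. The pupil-level analysis also uses separately recruited schools, which survey weights would not address.

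It is also fair to say that the survey's aim is exploratory and that the primary outcome is accelerometer-measured activity. Unweighted main results with a responder comparison are therefore defensible.

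**Conclusion.** The concern holds as a misstatement with a cheap remedy. The Abstract infers representativeness from invitation, limits the low-response caveat to other conurbations, and is out of step with the Discussion.

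The size of any bias cannot be known from the document. The illustrated 9, 8, 5 and 1 points rest on an assumed 10-point gap in the direction of implementers responding more, and on assumed response rates. They show that inviting every school gives no protection by itself when response is low or moderate; they do not show that the survey is biased. The primary pupil-level association and its power calculation are not affected by this point.

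**What to change.** Wording:
- Reword the strength to say that all 1826 state-funded primary schools in Greater London were invited.
- Extend the low-response limitation to Greater London itself, consistent with the Discussion, and state there whether survey schools, cross-sectional schools or both are meant.

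Analysis, which can still be settled because the data were being cleaned before analysis when the article was written:
- Report the survey response rate.
- Compare responders with the 1826 invited schools on public variables such as size, free school meals, ethnic mix, deprivation, Ofsted rating and borough.
- For research question 1, show response-weighted or raked prevalences and mean scores beside the unweighted ones as a sensitivity analysis, and state that weighting removes only the bias these variables explain.

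The cost is a small amount of linkage to public school data, one response model or raking step, and slightly wider confidence intervals for the weighted estimates. No new data collection is needed.

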#### School survey

Based on the WHO’s six domains of a whole-school physical activity approach (figure 2),^3^ we consulted with teachers to identify schools’ current practices and policies that support a physically active learning environment. We extracted relevant questions from previous studies of children’s physical activity, including SPEEDY,^18^ WAVES^19^ and GoActive,^20 21^ to capture whether schools support the delivery of a whole-school approach. We piloted the survey by asking primary school teachers to provide feedback on flow, response options, language, ease of understanding and the duration of completion. Any changes were reviewed and agreed by the authors and teachers. Two formats of our survey were created, an online version (using Qualtrics software) accessible via a link or QR code and a paper-based version (online supplemental file 2). Based on the responses from the survey, we will derive an ‘Active Environment Score’ for each school.

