### Sample size

The power calculation for this study used a multi-level model to account for the hierarchical structure of the data, with pupils (level 1) nested within schools (level 2). The model included random intercepts to capture variability between schools and examined the relationship between Active Environment Score (maximum score 50 points) and school day physical activity (in min). The analysis adjusted for key covariates such as sex (with females expected to engage in fewer than 10 min of physical activity), ethnicity, weekend physical activity, bioimpedance (used as a proxy for body composition), area deprivation and month of assessment (with higher activity expected during warmer months).

Based on the data collected to date, the sample size analysis included 600 pupils from 20 schools, with an average of 30 pupils recruited per school. The sample size of 600 pupils was the minimum number required for our power calculations; however, we aimed to recruit 1000 children to account for potential data losses (i.e., lost accelerometers, incomplete questionnaires, etc). 17 schools had preobserved Active Environment Scores ranging from 26 to 41, while the scores for the remaining three schools were simulated within this range for consistency.

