### Statistical analysis

All data collection for the study has been completed. The data are being processed and cleaned in preparation for the analysis. We will characterise features of our study population including child sex, ethnicity and adiposity. We will report characteristics of schools including school size, ethnic mix, Ofsted rating, percentage eligible for free school meals and area-based deprivation. We will present school and pupil level baseline characteristics by active environment scores with summary measures (totals, percentages, means and SD, medians and IQRs as appropriate).

The main analysis will treat the main outcome (physical activity during the school day) as a continuous variable. Decisions on valid accelerometer data to include in the analysis will be made when reviewing the data. We will use mixed-effects regression models to estimate the association between physical activity acceleration and the active school environment score. We will include pupil-level covariates (sex, ethnicity) and account for clustering at the school level by including random effects. Covariates will be included in the model in stages to assess how much each contributes to diluting or increasing the effect. To measure equity, the primary analysis will adjust for pre-specified school characteristics including school size, pupils eligible for free school meals, pupils whose first language is not English, children with Special Educational Needs and Disabilities and area-level deprivation. Sensitivity analysis will include clustering at the class-level within the school.

Results will be reported with a 95% CI. Mixed effects regression models as described for physical activity will be repeated for the outcomes of mental health and educational performance. All analyses will be carried out using Stata v18.5 and R statistical software. We will report our findings in line with the Strengthening the Reporting of Observational Studies in Epidemiology^33^ and Logical Explanations & Visualizations of Estimates in Linear mixed models guidelines^34^ for reporting cross-sectional studies.

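### With a school-level exposure, about 20 schools and up to five school-level adjusters, a random intercept alone does not secure accurate standard errors; REML with small-sample degrees of freedom should be stated

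*Protocol article*

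**What the plan says.** The strengths and limitations list in the Abstract of the protocol article says: "Multilevel mixed-effects regression models will include clustering of pupils by school, to allow for accurate standard errors and parameter estimates" when associations with the score are tested.

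The exposure is fixed per school. Under Outcomes and measures, School survey: "we will derive an ‘Active Environment Score’ for each school".

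Three statements bear on the number of schools:

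- Study setting and population gives the target: "recruit up to 1000 children from approximately 40 schools across Greater London".
- Sample size gives the number behind the power calculation, described as based on data collected so far: "the sample size analysis included 600 pupils from 20 schools, with an average of 30 pupils recruited per school".
- The same section adds: "17 schools had preobserved Active Environment Scores ranging from 26 to 41". The other three scores were simulated.

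Data collection is reported as complete, but the final number of schools is not given.

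In Statistical analysis, clustering is handled by school random effects and results come with 95% confidence intervals. On adjustment: "primary analysis will adjust for pre-specified school characteristics including school size, pupils eligible for free school meals, pupils whose first language is not English", followed by special educational needs and disabilities and area-level deprivation. On software: "All analyses will be carried out using Stata v18.5 and R statistical software". Neither ML nor REML is named, nor a normal or t reference.

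**The concern.** The score does not vary within a school, so its coefficient is in effect estimated from school means. Extra pupils make each school mean more precise but add no between-school degrees of freedom. Every school-level adjuster uses one up.

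Two separate problems follow when schools are few. ML estimates the between-school variance without allowing for the fitted school-level coefficients, so the standard error is too small. REML largely removes that bias. With either estimator, a multiplier of 1.96 treats the estimated variance as known and makes the interval too short.

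At stake are the 95% intervals for the main association, which are the planned form of inference. Intervals that are too narrow would make a chance association between score and activity look established. Results for mental health and educational performance are exposed in the same way, because the same models are to be repeated for them. The choice can also be made by default: Stata's linear mixed command fits by ML with normal-based intervals unless told otherwise (knowledge of the software, not a statement in the article).

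**Working it through.** **The plan's own figure.** The article states no type I error. It states 81% power at 0.55 min per score unit and over 90% at 0.70. Outcome SD, intraclass correlation (ICC) and covariate effects are not given, so the 81% cannot be rebuilt; only its consistency can be checked. The implied standard error is 0.55/(1.960 + 0.878) = 0.194. Power at 0.70 is then Φ(0.70/0.194 − 1.96) ≈ 95%, which agrees with the text. The stated power figures do not contradict each other.

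**Inputs for type I error**

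- J = number of schools: 20 and 17 (Sample size), 40 (target in Study setting and population).
- k = school-level adjusters: 5 (school size, free school meals, first language, special educational needs and disabilities, area deprivation).
- Two-sided 5%, taken from the 95% interval.
- Pupils per school: 30 for J = 17 and 20; 1000/40 = 25 for J = 40.
- ICC: not given; assumed 0.02 to 0.20.

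**Formulas** (balanced random-intercept model, variance estimate not truncated at zero)

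- Between-school degrees of freedom: df = J − 2 − k.
- REML with normal reference: P(|t_df| > 1.96).
- ML with normal reference: the ML variance is df/J times the REML one, so the error is P(|t_df| > 1.96·√(df/J)).

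**Numbers put in, k = 5**

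- J = 20: df = 13. REML: P(|t_13| > 1.96) = 7.2%. ML: 1.96·√(13/20) = 1.580, P(|t_13| > 1.580) = 13.8%.
- J = 17: df = 10. REML: 7.8%. ML: 1.96·√(10/17) = 1.503, P(|t_10| > 1.503) = 16.4%.
- J = 40: df = 33. REML: 5.9%. ML: 1.96·√(33/40) = 1.780, P(|t_33| > 1.780) = 8.4%.

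**Simulation check** (20,000 replicates per setting, independent school-level covariates, zero truncation included, range over the assumed ICCs)

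| Schools | ML, normal | REML, normal | t on between-school df |
|---|---|---|---|
| 20 | 9.9–13.9% | 6.1–7.3% | 4.1–5.1% |
| 17 | 10.4–16.2% | 6.3–7.7% | 3.7–4.9% |
| 40 | 7.9–8.6% | 5.6–6.1% | 4.8–5.2% |

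At 17–20 schools the mean ML standard error was 75–85% of the true one, and the REML standard error 97–100%. A likelihood-ratio test under ML does not escape the problem: 9.0–12.2% at 20 schools and 9.5–14.1% at 17.

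**Sensitivity to k.** If area deprivation is measured per pupil, k = 4. ML with a normal reference then gives 12.3% (20 schools, df 14) and 14.3% (17 schools, df 11); REML gives 7.0% and 7.6%. A sixth school-level term would raise ML to 15.5% and 18.8%. Month of assessment could be one: it is in the power model, and each school had a single data-collection time point. It is not listed in the analysis model.

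**The case against.** The strongest reply is that nothing in the article selects the inflated method. Estimator and degrees-of-freedom method are details that a condensed article commonly leaves to the analysis plan, which is not shown and may already prescribe REML with a correction. That stands: the omission is not the point. The point is a positive claim of accuracy that the documented design supports only on a condition the article does not state.

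Second, 20 is the number in the power calculation and 17 the number with scores at that time; the target was about 40. This also stands. At 40 schools the excess shrinks to about 8% (ML) or 6% (REML), though neither normal-based route reaches 5%.

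Third, under REML the standard error itself is nearly unbiased, so the quoted claim is close to right and what remains is mainly the multiplier. That is correct, and it is why ML and REML must be kept apart.

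A reader might infer more than this:

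- **That any large-sample inference gives 11–18% error.** The double-digit figures belong to ML only. With five adjusters the maximum is 16.4%; going beyond that needs a sixth school-level term.
- **That the fully adjusted model has far less power than the stated 81%.** This would need an assumed overlap between score and adjusters, which the article does not give. It also depends on the number of schools: at 40, power could exceed the stated figure.
- **That the power simulation adjusted for only one of the five.** The covariates in Sample size are introduced as examples, so the list is not exhaustive.

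**Conclusion.** The point holds in conditional form. With a school-level exposure, about 20 schools and up to five school-level adjusters, a school random intercept does not by itself guarantee accurate 95% intervals. The unqualified strengths statement is too strong at that number of schools. Against a nominal 5%, type I error is about 10–16% for ML with normal-based intervals at 17–20 schools, about 6–8% for REML with normal-based intervals, and about 5% with a t reference on between-school degrees of freedom.

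The figures assume balanced schools, adjusters that are constant within a school and an ICC between 0.02 and 0.20. How large the problem is in practice depends on the final number of schools and the fitting method, neither of which the article reports. The documents do not show that the intervals will be wrong, only that the stated ground for trusting them is insufficient. Because analysis has not started, a correction can still be fixed before results are seen.

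**What to change.** In Statistical analysis, state that the linear mixed models are fitted by REML, with Kenward–Roger or Satterthwaite degrees of freedom for the score coefficient and its 95% interval. Both named packages can do this (Stata: `mixed` with `reml` and `dfmethod(kroger)` or `dfmethod(satterthwaite)`; R: `lmerTest` or `pbkrtest`). Qualify the strengths statement so that accuracy is claimed for the random-effects model together with this small-sample correction, and report the final number of schools. Keep the pre-specified school adjusters; valid intervals do not require dropping any.

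The cost is one software option, a sentence or two, and somewhat wider intervals. Against REML with 1.96 the widening is about 10% at 13 df (2.160/1.96 = 1.10), 14% at 10 df (2.228/1.96 = 1.14) and 4% at 33 df (2.035/1.96 = 1.04).
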